## Discussion

This is the first randomized clinical trial to evaluate the effect of enhanced feedback and reward on arm rehabilitative training following stroke. Intrinsic (score, knowledge of performance) and extrinsic rewards (money) hypothetically improve motor cortex plasticity and overall motivation to train. Because motivation affects training time and time is a crucial determinant of effect [4], this trial controls for time by using a control intervention that is matched in time and dose of training.

In a motor learning study with healthy young subjects, we have shown that the consolidation/retention of a skilled motor task is more effective if the task was trained in the presence of reward [10]. In a rat model, projections from midbrain dopaminergic regions to M1 are required for successful motor learning and functional plasticity at cortical (layer II/III) synapses [15, 16], mechanisms that presumably support recovery after stroke [28]. Whether the dopaminergic system can be stimulated to improve recovery remains to be shown. Likewise, whether reward is an appropriate stimulus is yet unknown.

Previous studies have assessed the patient’s motivation for a specific training (e.g., Wittmann et al. [21] and Nijenhuis et al. [29]), but none of them compared the outcome to an appropriate control condition for the evaluation of the effectiveness of rewarding therapy. Although functional improvement itself might be motivating enough for some patients to train, here we are in search of a clinical effect of reward on a reduction in impairment (shoulder/elbow range of motion (ROM)) mediated by active and repetitive proximal-arm training. We chose this training method because (1) it can be standardized in its conduct and has quantifiable parameters of dose, movement success and arm workspace as primary outcome measure, (2) it is based on a therapy system which was already evaluated with patients and found to be safe, (3) it is easily supported in participating institutions without much training of therapists who provide assistance to the patient and (4) it has shown a moderate effect on chronically arm-impaired stroke survivors [21]. Because the ArmeoSenso training only works on proximal-arm function, it is not expected to have a clinically relevant effect on activities of daily living, independence, or quality of life. We therefore chose a primary outcome that is close to what is actually being trained, i.e., arm workspace. Workspace assessments have been widely used to assess the arm function of stroke patients, thereby showing high correlation to standard clinical scales [30, 31]. For a discussion of clinical relevance of functional outcomes, in the interest of clarity and conciseness, we would like to refer to the review by Ashford et al. [32]. Nevertheless, potential transfer to more clinical scores can be tracked using our secondary outcome measures.

The study is enrolling subjects during the initial 3 months after stroke. Most recovery is occurring in this period [33–37]. Therefore, we expect an improvement in arm function in both groups.

A positive outcome of this trial will emphasize the role of reward in rehabilitative training. This result could potentially be applicable to various forms of post-stroke rehabilitative training. Social rewards (smileys, praise), food rewards (sweets, dietary allowance), monetary reward or token programs are options that are easy to implement in situations where there is systematic interaction between a patient and a human trainer or a technical training device. Virtual-reality-based training games, therapy elements including repetitive performance feedback and similar approaches are examples where to integrate reward according to suggestions to be derived from the described study.

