**Methods:**

This multicentric, assessor-blinded, randomized controlled trial uses the ArmeoSenso virtual reality rehabilitation system to train 74 first-ever stroke patients (< 100 days post stroke) to lift their impaired upper limb against gravity and to improve the workspace of the paretic arm. Three sensors are attached to forearm, upper arm, and trunk to track arm movements in three-dimensional space while controlling for trunk compensation. Whole-arm movements serve as input for a therapy game. The reward group (*n* = 37) will train with performance feedback and contingent monetary reward. The control group (*n* = 37) uses the same system but without monetary reward and with reduced performance feedback. Primary outcome is the change in the hand workspace in the transversal plane. Standard clinical assessments are used as secondary outcome measures.

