### Study population

This study includes stroke patients (maximum 100 days after stroke) who meet the following criteria: minimum age of 18 years, hemiparesis of the arm due to cerebrovascular ischemia, the ability to lift the paretic arm against gravity, a minimal arm workspace of 20 cm × 20 cm in the horizontal plane, ability and willingness to participate, as well as the absence of severe aphasia (i.e., patients who are not able to follow two-stage commands), depression, dementia and hemianopia.

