### Randomization

The randomization procedure was planned and set up by an independent contract research organization (Appletree CI Group, Winterthur, Switzerland). A non-consecutively increasing, pseudo-randomly generated list of subject identification numbers (IDs) was created. IDs are chronologically assigned to each new study participant, stratified by the study center. Allocation to one of the two study groups is balanced in blocks of 4. The randomization list containing the subject ID, the corresponding group allocation and a randomly generated password was sent to an independent (unblinded) study staff member (“admin”) who has set up respective patient-user computer accounts used for accessing the therapy game. The group-specific version of the game, i.e., either with or without reward, is defined by the account. The admin keeps the assignment list and is not involved in data collection.

Immediately before the first training session, each study participant has to confirm by signature to have received a sealed envelope containing a butterfly etiquette with ID and password to access the account. The patient keeps this etiquette for the entire study duration.

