### Statistical analysis

Our primary analysis is an intention-to-treat analysis comparing the two groups. In addition, as this is an explanatory trial, a per-protocol analysis will be used to analyze the effect of feedback under ideal conditions [26, 27]. Therapy will take place in 15 sessions over 3 weeks, and there is the possibility that some subjects will not complete the full treatment regimen due to scheduling issues or other time constraints. If they still perform at least 12 h of therapy the data will be analyzed. All other patients will be considered “non-compliant” in the sense that they do not receive the full treatment dose. According to the per-protocol principle, their outcomes will not be analyzed.

A two-sample *t* test comparing the mean change in voxel workspace assessment between the two groups will be used; in case of non-normality, a Mann-Whitney test will be computed instead. Moreover, repeated measures analysis of variance (ANOVAs), in case of normally distributed data, or non-parametric Friedman tests will be used to assess the development of the different outcome measures over time. Statistical significance will be based on a *p* value threshold of 0.05. Data will be analyzed using MATLAB R2013b (or newer) (MathWorks Inc., Natick, MA, USA) and SPSS (version 23 (or newer), IBM Corp., Armonk, NY, USA).

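### Days since stroke, a known and plausible predictor of the 3-week workspace change, is used neither in allocation nor in the primary test; the cost is precision, not validity

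*Protocol article*

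**What the plan says.** **Entry window.** The Study population section reads: "This study includes stroke patients (maximum 100 days after stroke) who meet the following criteria". No lower limit is given. The abstract has the same upper limit: "74 first-ever stroke patients (< 100 days post stroke".

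**Expected recovery.** The Discussion states: "The study is enrolling subjects during the initial 3 months after stroke. Most recovery is occurring in this period". It then draws the consequence: "Therefore, we expect an improvement in arm function in both groups".

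**Allocation.** The Randomization section names one stratification factor, the centre: "IDs are chronologically assigned to each new study participant, stratified by the study center". It adds: "Allocation to one of the two study groups is balanced in blocks of 4".

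**Primary analysis.** The Statistical analysis section specifies a two-sample t test "comparing the mean change in voxel workspace assessment between the two groups", with a Mann-Whitney test if the data are not normal. Neither method takes a covariate, and none is named.

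**Sample size.** A difference of 4.8 voxels in change, a standard deviation of 7 voxels, two-sided alpha of 0.05 and 80% power give 35 per group, raised to 37 for 5% attrition. The effect size comes from unpublished pilot results. The section does not say which patients the standard deviation came from, or how long after stroke they were measured.

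**The concern.** The outcome is a change over 3 weeks, measured while patients are also recovering spontaneously. If most recovery falls early, as the Discussion says, a patient who starts soon after the stroke should on average gain more in those 3 weeks than one who starts near day 100, whatever the group. Variation in entry day then adds to the spread of the change score within each group and widens the confidence interval for the reward effect.

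The value that would remove part of this spread is a baseline quantity that every patient must have, because the 100-day limit cannot be checked without it. The article does not leave the method open for a later plan to fill in: it names an unadjusted test and an unadjusted fallback. At stake is how precisely a trial of 74 patients estimates its one primary contrast. The planned power leaves little reserve, since 35 evaluable patients per group only just reach 80%.

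**Working it through.** **Inputs from the Sample size section.** Difference 4.8 voxels, SD 7 voxels, 35 evaluable per group, two-sided alpha 0.05.

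**Input that is not in the documents.** R², the share of change-score variance explained by days since stroke. It is assumed here to lie between 0.05 and 0.30, and zero is shown as well.

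**Step 1: reproduce the plan.** The standard error of the difference is 7 × √(2/35) = 1.67 voxels. The noncentrality is 4.8 / 1.673 = 2.87 on 68 degrees of freedom. The exact noncentral-t power is 80.7% (34 per group gives 79.6%). For attrition, 35 / 0.95 = 36.8, so 37. The stated 35 and 37 both reproduce.

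**Step 2: does omitting the covariate bias the test?** In 20,000 simulated trials with 35 per arm, entry was uniform over days 14 to 100, the total SD was 7 and the covariate was left out. The type I error was 5.2% at R² = 0.10 and 4.9% at R² = 0.30. Power at a true difference of 4.8 was 80% to 81%. The planned test is valid and keeps its planned power.

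**Step 3: how far can the groups differ in entry day by chance?** With entry assumed uniform from day 7, 14 or 20 up to day 100, the SD is (100 − start)/√12 = 26.8, 24.8 or 23.1 days. The standard error of the difference in means is SD × √(2/35) = 6.4, 5.9 or 5.5 days, which gives a 95% range of about ±11 to ±13 days. If the SD of 7 voxels is the total spread, the 1.67-voxel standard error already covers the effect of such imbalance.

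**Step 4: what adjustment would gain, if SD 7 includes this variation.** The residual SD is 7 × √(1 − R²), with one degree of freedom fewer (67).

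| Assumed R² | Residual SD | Power at 35 per group | n per group for 80% |
|---|---|---|---|
| 0 | 7.00 | 80.7% | 35 |
| 0.05 | 6.82 | 82.7% | 33 |
| 0.10 | 6.64 | 84.6% | 32 |
| 0.20 | 6.26 | 88.5% | 28 |
| 0.30 | 5.86 | 92.2% | 25 |

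The table ignores the small variance inflation from chance imbalance of the covariate. On average this is a factor of about 1 + 1/(70 − 4) = 1.015. Including it lowers each power by about 0.4 to 0.6 percentage points; at R² = 0, power becomes 80.1%.

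**Step 5: sensitivity, if SD 7 leaves this variation out.** The total SD would be 7/√(1 − R²). At R² = 0.05, 0.10, 0.20 and 0.30 the unadjusted test would then have 78.7%, 76.5%, 71.5% and 65.8% power at 35 per group. The documents do not show that this case applies.

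**The case against.** The strongest reply is that nothing here is an error. Randomization balances days since stroke in expectation, recovery common to both groups cancels in the difference, and an unadjusted comparison of change scores is a valid primary analysis. Power meets the stated 80%, so any gain is power above target. Covariates are also often settled in an analysis plan that is not shown. Most of this stands: the point concerns efficiency only. The last argument carries less weight, because the article does fix the primary test, and a later plan that added a covariate would depart from it.

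Three stronger readings are tempting, and the documents do not support them.

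- **That uneven recovery biases the reward contrast.** Step 2 shows that it does not. Chance imbalance is part of the error that the t test already allows for.
- **That the trial is underpowered.** This follows only if the SD of 7 voxels leaves out variation in entry day, for example if it came from chronic patients. The Discussion links the earlier trial of the same system to chronic patients, but the Sample size section does not say that the SD came from that trial.
- **That enrolment to day 100 breaks the rationale of the initial 3 months.** The gap is about 9 days (100 against about 91). The Discussion sentence supports only the expectation that both groups will improve, and no eligibility rule, endpoint or sample-size figure depends on it. The spread in recovery would be almost the same with a 91-day limit.

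One could also model spontaneous recovery as an explicit curve and obtain large ratios between early and late entrants. The shape, the time constant and the mean gain would all be assumptions, so no such ratio is relied on here.

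**Conclusion.** The point holds as a precision improvement. The protocol fixes an unadjusted primary test while itself naming a reason why days since stroke should predict the outcome, and it must know that value for every patient. The test is valid and reaches its stated power if the SD of 7 voxels is the total spread. Adjustment would raise power from about 81% to about 83% at R² = 0.05 and about 92% at R² = 0.30. With an uninformative covariate it would stay at 80% to 81%. The size rests entirely on R², for which the documents give no figure; the Discussion supports the direction but not the amount. The 3-month and 100-day wordings should be aligned as a clerical matter.

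**What to change.** Replace the unadjusted primary comparison with a pre-specified linear model (ANCOVA): workspace change as the outcome, group as the factor, and days from stroke to first training session, on the log scale, as a baseline covariate. The two-sample t test can be kept as a sensitivity analysis. The Mann-Whitney fallback cannot carry the covariate, so the plan should also say what replaces it if the model's residuals are clearly non-normal.

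The cost is a sentence or two in the Statistical analysis section and one degree of freedom. No new data are needed, because the date of stroke is required for eligibility. At submission 16 of the 74 patients had been enrolled, so the change could still be specified well before the data were complete.

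Separately, and only as a wording correction, bring the Discussion's description of the enrolment period into line with the limit in the abstract and the Study population section.

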### Trial status

The trial is currently recruiting patients. At the time of submission, 16 stroke patients have been enrolled.

## Abbreviations

AEs: Adverse events
BI: Barthel Index
EKNZ: Ethikkommission Nordwest- und Zentralschweiz
FMA-UE: Fugl-Meyer Assessment of the upper extremity
GCP: Good Clinical Practice
IDs: Identification numbers
IMU: Inertial measurement unit
M1: Primary motor cortex
MAL14: Motor Activity Log 14
mRS: modified Rankin Scale
NIHSS: National Institutes of Health Stroke Scale
PIs: Principle investigators
RCT: Randomized controlled trial
ROM: Range of motion
SAEs: Serious adverse events
VR: Virtual reality
WMFT: Wolf Motor Function Test
